### Randomization, allocation concealment, and blinding

The eligible participants will be randomly assigned to the groups: SEG (*n* = 30), SSG (*n* = 30), SCG (*n* = 30), which will perform the corresponding exercise program 3 days a week compared to the CG (*n* = 30), which will not carry out a supervised exercise program. The method to generate the 1:1 allocation sequence to one of 4 experimental groups will be computer-generated random numbers (Research Randomizer). The assignment will be made using previously constructed balanced blocks until a total of 120 participants are assigned with the same number of participants per experimental group.

All participant assignment keys will be saved in a confidential file in the Campus Docent Sant Joan de Déu. An alphanumeric code will be assigned to each experimental group to guarantee masking. Once this process is completed, participants will be assigned to the corresponding experimental group. The alphanumeric code will be known by one of the researchers and will not be disclosed to the rest of the researchers until the analysis of the interventions is completed. Due to the characteristics of the intervention process in each experimental group, participants cannot be blinded to the exercise training programs. However, researchers and collaborators will be blinded to participant data during the baseline, intervention, and assessment processes. Blinding will be performed for all data.

The design of this project will include measurements of four relevant dimensions (Fig. 1): 1) Cardiorespiratory fitness; 2) Muscle fitness; 3) Pain and mental health; and 4) Biomarkers of inflammation and oxidative stress. In all cases, differences which may derive from variables of sex and gender will be considered.

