#### Transversal objectives (TO)

TO1. Consider the perspective of sex and gender in all the SO.

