### Participants and criteria of eligibility

The sample will be made up of 120 eligible participants, over the age of 60 years who have had COVID-19 disease and present persistent COVID-19 symptomatology with sequelae of fatigue, muscle weakness, pain, difficulty in performing daily life activities, etc. diagnosed by the corresponding physician.

Participants will be recruited from internal medicine services and patients with post-COVID-19 sequelae will be selected from the database of the hospital and primary care centers who have given their consent to be contacted for participation in the research project. The recruitment status of the participants will be ongoing at the time of manuscript submission.

Candidates will fulfill the following inclusion criteria:Persons of both sexes (and different expression of gender) older than 60 years of age.Molecular diagnosis (reverse transcription polymerase chain reaction [RT-PCR]) of infection by SARS-CoV-2.No history of physical diseases and no disease or disability that limits participation in the exercise program or precludes the corresponding measurement/evaluations.Be able to communicate without difficulty.Be able to understand the objectives of the project and provide written, informed consent.Not taking any medication that can affect normal performance of the exercise program and the evaluations. Specifically, patients who were treated with IL-6 receptor antagonists (example: tocilizumab) during the last month will be excluded. This type of medications will interfere with the exercise adaptations of the cardiorespiratory system.

The following exclusion criteria will apply:Having acute or terminal disease or any other disease that may affect the normal practice of a supervised exercise program and the corresponding evaluations.Consumption of any amount of alcohol or drugs during the study.Be performing any type of activity that may interfere in carrying out the supervised exercise program or the evaluations.Not completing the study once initiated or wishing to participate in the control group.

To calculate the sample size of this project a type 1 (α) error of 5% and a 95% confidence interval with a level of precision (d = 0.095) was established for the test of proportional hypotheses resulting in a sample size of *n* = 108 persons, increased by 10% (rounded up to *n* = 120) to compensate for possible dropouts along the study period.

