#### Primary outcomes

##### Cardiorespiratory and muscle fitness

A series of functional physical condition used in the scientific community especially in older persons will be used [29]. At present, this series of tests has reference values for different age ranges from 60 to 94 years and cut-off points for each test associated with physical independence [30].

Aerobic capacity: this will be measured with the 6-min walk test, measuring the maximum distance (meters) walked in 6 min by the participants [29].

In addition, to complete the evaluation of cardiorespiratory fitness of the older adults, an incremental protocol on a cycle ergometer will be carried out using a respiratory gas analyzer. Depending on the characteristics of the participants, adapted standard protocols will be used [31–34].

Lower limb strength: this will be evaluated with the sit and stand test for 30 s. The number of times in 30 s the participant can completely stand up from a seated position with the back straight and the feet on the floor without pushing with the arms will be counted. A test will be performed to become familiarized with the test [29].

In addition, a test will be carried out to evaluate the explosive strength of the lower limbs by performing 3 countermovement jumps with 30 s of rest between each jump on a force platform (Musclelab, Ergotest Technology AS, Langesund, Norway) [35].

Upper limb strength: This will be evaluated with the bicep curl test made with a 2 kg weight for women and a 4 kg weight for men. The number of elbow curls made in 30 s with each upper limb will be counted [29].

Hand grip strength: This will be evaluated with the hand grip strength test. This test will be done with a digital dynamometer [36]. The participants will remain in the standard bipedal position throughout the test with the arm in full extension. Each participant will perform the test twice (alternatively with the two hands) with a 1-min rest period between each measurement.

Motor Agility/Dynamic balance: This will be evaluated with the 8-foot up and go test. The patient must get up from a chair, walk 8 feet towards and around a cone and return to the chair in the shortest time possible [29]. The best of two attempts will be registered.

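### The described block allocation equalises arm size only and names no sex stratum, although sex and gender are to be considered in every specific objective; block within sex and adjust for it

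*Protocol article*

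**What the plan says.** **Objective.** The protocol article, under Transversal objectives, states: "TO1. Consider the perspective of sex and gender in all the SO". There are six specific objectives (SO1 to SO6). The section on randomization, allocation concealment and blinding repeats the aim for the four measured dimensions: "In all cases, differences which may derive from variables of sex and gender will be considered".

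**Allocation.** The same section gives the generator, "The method to generate the 1:1 allocation sequence to one of 4 experimental groups will be computer-generated random numbers (Research Randomizer"), and the restriction, "The assignment will be made using previously constructed balanced blocks until a total of 120 participants are assigned with the same number of participants per" arm, which means 30 in each. It gives no block size, number of lists or stratification factor.

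**Eligibility.** Entry is open to "Persons of both sexes (and different expression of gender) older than 60 years of age", with no quota and no expected share of women.

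**Outcomes and analysis.** One of the primary fitness tests, upper limb strength, uses a sex-specific load: "This will be evaluated with the bicep curl test made with a 2 kg weight for women and a 4 kg weight for men". Under Process of evaluation, the effect is the 12-week value compared with the value before the programme. Under Data collection, management and analysis, the gender perspective is attached to the descriptive statistics. The between-group comparison is described only as parametric or non-parametric, with no sex term.

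**The concern.** Sex is known before allocation and is the one participant characteristic that the plan singles out for every specific objective. The allocation is described in some detail, and the only thing it is said to balance is the number per arm. Blocks that ignore sex do nothing to balance sex. With 30 per arm, chance alone can leave two programmes with clearly different proportions of women.

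Three things are at stake:

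- **Precision of the programme comparison.** This arises where women and men respond differently, or where raw post-test values are compared.
- **Cell sizes for TO1.** If recruitment leans towards one sex, an arm may hold very few of the other.
- **No stated remedy in the analysis.** On the text shown, sex enters neither the allocation nor the comparison between arms.

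**Working it through.** **Plan's own sample size.** This check only confirms the 120 used below. n = z² × p(1−p) / d² with z = 1.96, d = 0.095 and p = 0.5 (p is assumed, as none is stated) gives 3.8416 × 0.25 / 0.009025 = 106.4, so 107 against the stated 108. With 10% dropout, 108 / 0.90 = 120, or 30 in each of four arms.

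**Inputs.** N = 120 and 30 per arm, from the randomization section. The share of women is assumed to be 50%, 60% or 70% (60, 72 or 84 women). By symmetry, the gaps between arms for 30% and 40% women match those for 70% and 60%.

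**Model.** Allocation ignores sex, so the numbers of women in the four arms follow a multivariate hypergeometric distribution.

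- Variance of women in one arm: 30 × p(1−p) × 90/119. At p = 0.5: 7.5 × 0.7563 = 5.67, SD 2.38.
- Two arms have covariance −1/3 of that variance, so the variance of their difference is (8/3) × 5.67 = 15.13, SD 3.89 women. That is 3.89/30 = 13 percentage points, with a 95% range of about ±25 points.

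| Share of women (assumed) | A given pair differs by ≥6 (20 points) | Some pair of the four differs by ≥6 | Some pair differs by ≥8 | Some arm has ≤6 men |
|---|---|---|---|---|
| 50% | 16% | 49% | 21% | <0.1% |
| 60% | 15% | 47% | 20% | 3% |
| 70% | 12% | 41% | 15% | 47% |

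The probabilities were simulated and agree with exact enumeration.

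**With separate block lists for women and men.** The largest gap between any two arms is at most 1 woman with blocks of 4 and at most 2 with blocks of 8, that is 1/30 to 2/30, or 3 to 7 points. Without them, the median largest gap is 5 women (17 points) and the 95th percentile is 9 to 10 women (30 to 33 points).

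**Effect on a raw post-test mean.** The shift equals the imbalance times the sex difference. The documents give no sex difference for any test. If it is assumed to be 1 to 2 within-sex SD, a 20-point imbalance shifts the contrast by 0.20 × 1 = 0.2 SD to 0.20 × 2 = 0.4 SD. In pre-post change a constant sex difference drops out, and only a sex difference in the change itself is carried through.

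**Effect on the arm-by-sex estimate for two arms.** SE = √(1/a + 1/(30−a) + 1/b + 1/(30−b)) in SD units, where a and b are the numbers of women.

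- a = b = 15: √(4/15) = 0.516.
- a = 20, b = 10: √0.30 = 0.548, about 6% larger.

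**Effect on a thin cell.** With 70% women there are 36 men, or 9 per arm when stratified. Comparing men between two arms, the SE is √(1/9 + 1/9) = 0.471 SD with 9 and 9, and √(1/6 + 1/9) = 0.527 SD with 6 and 9, about 12% larger.

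**The case against.** The strongest reply is that this is an efficiency choice made to look like a flaw. Several parts of that reply stand, and they rule out stronger readings that a reader might infer.

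- **A single unstratified list.** The article does not say this. It is an inference from silence and from the equal total per arm, and the full protocol is not shown. The point is therefore conditional on the blocks not already being built within sex.
- **Sex imbalance confounds the comparison.** It does not. Unstratified randomisation is valid, the comparison is unbiased over repeated allocation, and the usual standard errors already reflect chance imbalance. Adjusting for sex recovers most of what stratifying would give.
- **An even chance of a large gap.** The 41% to 49% refers to the most extreme of six pairs. It is relevant because the trial asks which programme is most effective, but for one named pair the figure is 12% to 16%.
- **TO1 cannot be answered.** The plan promises to consider sex and gender, not a powered subgroup comparison. Moderate imbalance raises the arm-by-sex SE by only about 6%. Few men in an arm becomes likely only at the skewed 70% assumption, and even then stratifying gives no more than 9.
- **The biceps-curl loads prove the case.** They show that the plan itself treats the sexes differently on a primary test. But stratified arms would still pool 2 kg and 4 kg counts, and each participant's pre-post change uses one load.
- **Grip and jump tests are strongly sex-dependent.** The documents give no figure for either, so nothing here rests on them.

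The reply also says that covariates belong in an analysis plan, which is not shown. A missing model is no fault in itself. It matters here only because the allocation as described leaves sex to the analysis, and the analysis text that is shown uses gender for description only. The reply does not remove the main point: the scheme as described balances arm size alone, while a declared cross-cutting objective concerns a factor known at entry.

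**Conclusion.** The point holds as a cheap improvement in precision, not as an error that invalidates the trial. As described, the allocation equalises arm size and names no sex stratum, and the analysis text shown does not make up for it. The sizes rest on two assumptions: 50% to 70% women, and blocks that ignore sex. On these, a 20-point gap in the share of women arises for a given pair of arms in about 12% to 16% of trials and for some pair among the four in about 41% to 49%. A very small male cell (6 or fewer in some arm) is a real prospect only near 70% women, at about 47%. The consequences are confined to sex differences in response, comparisons of raw post-test values and thin sex cells for TO1.

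**What to change.** 1. State whether the balanced blocks are built within sex. If they are not, construct them separately for women and men in the same 1:1:1:1 ratio. The article describes recruitment as ongoing at submission, so for participants already allocated nothing changes and the separate lists apply from now on.
2. In either case, include sex and the baseline value as covariates in the between-arm comparison.
3. Report arm-by-sex estimates with confidence intervals for TO1, labelled exploratory.

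The cost is a second randomisation list and one or two model terms. Arm totals may also depart slightly from exactly 30 when the last block in a sex stratum is incomplete, so the wording on equal numbers per arm should allow for this.

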### Program of supervised exercise

The intervention will consist in a program of supervised physical exercise performed 3 times a week for 12 weeks. For the planning and control of the exercise program the progressive individualized planning model will be applied based on the subjective perception of effort and cardiorespiratory parameters (heart rate and ventilatory threshold determined in the evaluation tests) of the participants. This program has been used by our research group in previous studies for improving cardiorespiratory and muscle fitness [28]. The basis of this periodization model establishes an initial period of individualization to obtain the personal parameters used for the training load.

Patients with post-COVID-19 sequelae will be randomly assigned to 3 programs of supervised exercise (Table 1).

**Table 1 Tab1:** Summary of the characteristics of the supervised exercise programs

Session	EG	Methodology	WF	Dur (min)	NE	Set	Rep/T	Rest E/S	Intensity
Warm-up		General/ JM	3 s/w	5	1–3	1	5–15/20 s	15/60–120 s	HR: 40–50% RPE: 4–5
Workout	SET	Walking	3 s/w	50	1	1	1	––	HR to VT1:50–75% RPE: 4–8
	SST	Circuit training	3 s/w	50	10	1–4	5–25/60 s	15/60–120 s	HR to VT1:50–75% RPE: 4–8
	SCT	Walking + Circuit training	3 s/w	15 + 35	1 + 6–8	1 + 1–3	1 + 5–25/60 s	–– + 15/60–120 s	HR to VT1:50–75% RPE: 4–8
Cooling down		Stretching/ Relaxation	3 s/w	5	1–8	1	20–30 s	15/60–120 s	Resting HR RPE 1–3

*Abbreviations*: *Dur* Duration (minutes), *EG* Experimental group, *E/S* Exercise/set, *HR* Heart rate, *JM* Joint mobility, *NE* Number of exercises, *Rep/T* Repetitions/effort time, *RPE* Ratio of perceived exertion, *s/w* Sessions/weekly, *SCT* Supervised concurrent training, *SET* Supervised endurance training, *SST* Supervised strength training, *VT1* First ventilatory threshold, *WF* Weekly frequency

#### Program of endurance exercise

The program of supervised endurance exercise will consist in walking for 1 h 3 times a week. The intensity (step speed) will gradually be increased each week (approx. 5%) according to the perception of the participant. A pulsometer will be used to determine the safe range of heart rate at which the participant should perform.

#### Program of strength exercise

This will consist in performing a program of traditional strength 1 h 3 times a week. Circuit training methodology will be used (10 exercises) alternating muscle groups of the upper and lower extremities and trunk. The initial series be of 1 exercise, evolving to up to 3–4 along the program based on the individual adaptation of the individual. The intensity (load applied) will be gradually increased each week while the recovery times between each exercise activity will be reduced (approx. 5%) according to the perception of the participant. A pulsometer will be used to determine the safe range of heart rate at which the participant should perform.

#### Program of concurrent exercise (endurance and strength)

The participants will perform 1 h of concurrent exercise, combining walking (20 min) and the strength program for 40 min, maintaining the same instructions explained previously in each exercise program.

#### Control group

The control group will not carry out any supervised exercise program but will maintain their same habits of daily life activities.

Each supervised exercise session will include 10 min of general warm up and mobility exercises. For quality adequate control of the program and to stimulate the practice of collective exercise, the sessions will be performed in groups of 10–15 participants. Different strategies will be used to improve program adherence and fulfillment. The participants of the intervention groups of the project will be informed of the importance of attending all the sessions of supervised exercise as well as the evaluations made before and after the intervention period. In addition, a series of motivation strategies will be established for the participants of the intervention groups to increase or maintain the index of adherence to the exercise program including group dynamics to improve cohesion among the participants.

The CG will be supervised by a weekly phone call made by the members of the research group will the aim of knowing their health status and inform them of the evaluation periods and any other aspect that the participants consider relevant.

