##### Mental health

Psychosocial variables will be evaluated using the Hospital Anxiety and Depression Scale (HADS) [37], which is made up of 7 items for anxiety and depression. Each item of the anxiety subscale (HADS-A) and the depression subscale (HADS-D) will be scored on a scale of 4 points from 0 (none) to 3 (much more). The highest scores indicate the highest levels of anxiety or depression.

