## Discussion

The present project aims to evaluate the effects of different exercise programs of physical and mental health, physical condition and biomarkers of the immune system and oxidative stress in older patients with post-COVID-19 sequelae.

COVID-19 has left its stamp on the world, affecting more than 100 million persons, and although the data are confounding, there have been around 15 million deaths according to the World Health Organization [39]. In Spain, up to August 9, 2022, 13,280,557 confirmed cases of COVID-19 and 111,339 deaths had been reported (https://www.sanidad.gob.es/profesionales/saludPublica/ccayes/alertasActual/nCov/documentos/Actualizacion_623_COVID-19.pdf).

Most of the persons presenting COVID-19 survive, but it is also true that many of the survivors present the so-called post-COVID-19 sequelae. Older persons are more susceptible to presenting these sequelae, especially those with associated comorbidities, subsequently affecting their quality of life [11] and increasing the risk of death [12–14].

Physical exercise has demonstrated to be one of the most beneficial regimens for short-, medium- and long-term health in all types of populations. It prevents, delays, mitigates and even reverses many metabolic, pulmonary, cardiovascular, neurocognitive, inflammatory, rheumatic and musculoskeletal diseases, reducing fatigue and pain and increasing tolerance to exercise and daily life activities [18–23]. In addition, it improves physical and mental health in older persons, especially in those who have had COVID-19 [24].

The EJerSA-COVID-19 project is clearly in line with the “Health, Demographic Change and Well-being” challenge of the Ministry of Health, given the implications that are expected to be obtained in the prevention of the consequences of ageing through physical exercise, and especially, in patients with post-COVID-19 sequelae. The interdisciplinary approach of this project aims to generate knowledge that can be transferred and applied to favor healthier aging in older persons, with special emphasis on health problems related to age and COVID-19 that have negative repercussions on cognitive, physical and mental status. As stated within the setting of this grant call, this project will cover 3 main axes:Influence of physical activity that is beneficial to health on chronic non transmittable diseases (Post COVID-19)Impact of physical exercise on psychological well-being.Empowerment of the people: Active environments.

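### Cohesion activities, motivation strategies and the stress on attending evaluations go to the exercise arms only, so HADS and SF-36 contrasts with control measure the supervised group programme, and encouragement to attend Post differs by arm

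*Protocol article*

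**What the plan says.** The relevant text is in the Control group section of the Methods, which also describes how the exercise sessions are delivered.

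- **Format.** For the exercise arms, "the sessions will be performed in groups of 10–15 participants".
- **Motivation.** In these arms "a series of motivation strategies will be established for the participants of the intervention groups to increase or maintain the index of adherence", "including group dynamics to improve cohesion among the participants".
- **Message on attendance.** "The participants of the intervention groups of the project will be informed of the importance of attending all the sessions of supervised exercise", and the sentence continues "as well as the evaluations made before and after the intervention period".
- **Controls.** They keep their usual daily habits. "The CG will be supervised by a weekly phone call made by the members of the research group". The call asks about health status, informs them of the evaluation periods and covers anything else they find relevant.

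Participants cannot be blinded (Randomization, allocation concealment, and blinding). HADS and SF-36 are questionnaires listed under Secondary outcomes. Outcomes are compared between one Pre and one Post evaluation at 12 weeks (Process of evaluation).

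**The concern.** The arms differ in more than exercise. Exercise participants meet in a group three times a week and receive deliberate cohesion building and motivation; controls have an individual call. Company and attention could plausibly move anxiety, depression and quality-of-life scores in people who know their allocation. If so, a favourable HADS or SF-36 contrast with control could be read as a benefit of exercise when part of it came from the group setting. The Conclusions section invites that reading, since it speaks of physical exercise therapy improving mental health.

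The second issue concerns data collection. Being told that an evaluation matters is a stronger prompt than being told when it takes place. With only one follow-up evaluation, a participant who misses Post supplies no follow-up value. If the prompt affected attendance, missing outcomes would differ between control and the exercise arms, on the primary outcomes as well as the questionnaires.

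**Working it through.** The plan gives no figure on this point, so there is none to reproduce. The check sets the arms side by side and counts scheduled contact.

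**Arm by arm (Control group section)**

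| Element | Exercise arms | Control |
|---|---|---|
| Staff contact | group sessions of 10–15 people | individual weekly call |
| Motivation strategies | yes | none stated |
| Cohesion activities | yes | none stated |
| Evaluations | told that attending matters | informed of the evaluation periods |

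**Contact count**

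1. Exercise arms: 3 sessions a week x 12 weeks (Program of supervised exercise) = 36 sessions. At 5 + 50 + 5 = 60 min each (Table 1), this is 36 h.
2. Control: one call a week x 12 weeks = 12 calls, assuming that the calls span the intervention period.
3. Ratio of contacts: 36 / 12 = 3.
4. Ratio of time: call length is not stated. At an assumed 5 to 10 min, 12 calls take 1 to 2 h, so the ratio is 36 / 2 = 18 to 36 / 1 = 36.

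The time ratio describes the imbalance in contact and is not an estimate of bias. The 36 h include the exercise itself, which is the intervention, and nothing in the documents converts hours of contact into HADS or SF-36 points.

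**Missing data**

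The dropout allowance raises the total from 108 to 120 (Participants and criteria of eligibility), that is 120 - 108 = 12 people over all four arms. No split by arm is given or assumed, so differential attrition cannot be calculated.

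**Which contrasts are affected**

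The contact and motivation issue affects contrasts with control. SEG, SSG and SCG share the same group format, number of sessions and strategies, so contrasts among them are not exposed to it. Those contrasts say only whether one mode differs from another. If all three modes improved HADS equally, they would show nothing, whatever the benefit of exercise.

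The Limitations section adds a fallback: if recruitment falls short, combined exercise is compared with control alone. Only the contrast that mixes exercise with group contact would then remain.

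**The case against.** The strongest reply is that the trial asks about programmes. Study design asks which supervised exercise program is most effective compared with control, the Specific objectives speak of the effectiveness of different exercise programs, and Process of evaluation speaks of the effects of the program. Group delivery is openly part of that programme, and a usual-habits control is a legitimate choice. This stands. The contrast with control is a valid estimate of the programme as delivered, and no attention-control arm is needed. What remains is that the mental-health conclusion should be worded for the programme.

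A reader might take the Discussion line "Impact of physical exercise on psychological well-being" as a planned claim about exercise alone. It does not support that: it is one of three themes taken from the grant call, and sets no rule of inference for HADS.

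A reader might also infer that controls are not contacted about evaluations, or that their Post data will be missing more often and so bias every contrast with control. The documents support neither. The weekly call covers the evaluation periods, and it offsets part of the difference in attention. The article does not give the call script and does not say that controls are never told that evaluations matter. The direction of any imbalance is also open: the exercise arms carry 36 sessions, and the Limitations section names illness, lack of motivation and symptoms as reasons for dropout. What stands is the stated difference between the two messages.

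**Conclusion.** The point holds in a limited form. As written, motivation strategies, cohesion activities and the stress on attending Pre and Post are directed to the exercise arms, and controls are informed of the evaluation periods by phone. This creates a risk of differential missing data that the documents neither show nor allow to be sized. A HADS or SF-36 difference from control is the joint effect of exercise, group contact and motivation. The count of 36 sessions against about 12 calls rests on the calls lasting 12 weeks; the 18- to 36-fold time ratio rests further on an assumed call length.

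Two stronger readings should be avoided. The control contrast is not invalid, because it estimates the supervised programme. Contrasts among SEG, SSG and SCG are not a cleaner test of exercise itself, because all three arms exercise. The attribution issue concerns secondary, self-reported outcomes; the argument is not made for the performance tests and biomarkers listed as primary.

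**What to change.** 1. Give all four arms an identical message on the importance of attending the Pre and Post evaluations. For controls, use the weekly call that they already receive; if the calls begin only after Pre, give the Pre part at enrolment to everyone. This has to be in place before the Post evaluations, because analysis cannot restore visits that did not take place.
2. State that the HADS and SF-36 contrasts with control estimate the effect of the supervised group programme as delivered, including in the fallback comparison of combined exercise with control described under Limitations. Word the mental-health statements in the Conclusions section to match.
3. Present contrasts among SEG, SSG and SCG as differences between exercise modes only.

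The cost is one sentence in the call script and a slightly narrower conclusion for the self-reported outcomes, with no extra visits or staff.
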